## Abstract

**Background:**

Depression and anxiety are common mental health disorders worldwide. The UK’s Improving Access to Psychological Therapies (IAPT) programme is part of the National Health Service (NHS) designed to provide a stepped care approach to treating people with anxiety and depressive disorders. Cognitive Behavioural Therapy (CBT) is widely used, with computerised and internet-delivered cognitive behavioural therapy (cCBT and iCBT, respectively) being a suitable IAPT approved treatment alternative for step 2, low- intensity treatment. iCBT has accumulated a large empirical base for treating depression and anxiety disorders. However, the cost-effectiveness and impact of these interventions in the longer-term is not routinely assessed by IAPT services. The current study aims to evaluate the clinical and cost-effectiveness of internet-delivered interventions for symptoms of depression and anxiety disorders in IAPT.

**Methods:**

The study is a parallel-groups, randomised controlled trial examining the effectiveness and cost-effectiveness of iCBT interventions for depression and anxiety disorders, against a waitlist control group. The iCBT treatments are of 8 weeks duration and will be supported by regular post-session feedback by Psychological Wellbeing Practitioners. Assessments will be conducted at baseline, during, and at the end of the 8-week treatment and at 3, 6, 9, and 12-month follow-up. A diagnostic interview will be employed at baseline and 3-month follow-up. Participants in the waitlist control group will complete measures at baseline and week 8, at which point they will receive access to the treatment. All adult users of the Berkshire NHS Trust IAPT Talking Therapies Step 2 services will be approached to participate and measured against set eligibility criteria. Primary outcome measures will assess anxiety and depressive symptoms using the GAD-7 and PHQ-9, respectively. Secondary outcome measures will allow for the evaluation of long-term outcomes, mediators and moderators of outcome, and cost-effectiveness of treatment. Analysis will be conducted on a per protocol and intention-to-treat basis.

**Discussion:**

This study seeks to evaluate the immediate and longer-term impact, as well as the cost effectiveness of internet-delivered interventions for depression and anxiety. This study will contribute to the already established literature on internet-delivered interventions worldwide. The study has the potential to show how iCBT can enhance service provision, and the findings will likely be generalisable to other health services.

**Trial registration:**

Current Controlled Trials ISRCTN ISRCTN91967124. DOI: 10.1186/ISRCTN91967124. Web: http://www.isrctn.com/ISRCTN91967124.

Clinicaltrials.gov: NCT03188575. Trial registration date: June 8, 2017 (prospectively registered).

## Background

According to the Global Burden of Disease (GBD) study, depression and anxiety disorders contribute the highest degree of disability amongst all mental and substance abuse disorders [1]. Both anxiety and depressive disorders contribute to increased societal costs through higher health care utilisation [2, 3], as well as absenteeism from work [4]. In Europe, the total cost of mood disorders in 2010 was €113.4 billion, comprising direct health care costs and indirect costs including unemployment, sickness benefit, lost productivity, and early retirement [5]. In England, approximately 1 in 6 adults have a common mental disorder [6], and mental health disorders / difficulties have been estimated to represent 23% of the total cause of disability, higher than other conditions such as cancer and CHD [7].

### Treatment of depression and anxiety

Psychological therapies have been demonstrated to be equally as effective as anti-depressant medication [8] and a recent meta-analysis of 34 studies shows a consistent patient preference for psychological vs. pharmacological treatment [9]. Furthermore, psychological therapies such as Cognitive Behavioural Therapy (CBT) have been shown to be clinically and cost effective [10, 11] and has demonstrated effectiveness in treating, maintaining progress, and preventing relapse in both depression and anxiety disorders [12–15].

Psychiatric disorders are seldom the principal reason for GP visits, and yet in one primary care study, depression was encountered in upwards of 31% of consultations, with anxiety detected in approximately 19% of consultations [16]. However, once identified, a multitude of factors prevent individuals from accessing evidence-based psychological interventions, including long waiting lists and a shortage of trained professionals [17]. A number of studies have investigated how depression and anxiety disorder treatment in primary and specialised care settings can be improved [18] by means of ‘collaborative care’ [19], ‘disease management’ approaches, and ‘stepped care’ initiatives [20]. Within stepped care, professionally guided low-intensity self-help interventions have become an attractive evidence-based alternative. Low-intensity interventions refer to those that require less time with a specialist therapist and include bibliotherapy, guided self-help, and internet-delivered CBT interventions [21].

### Improving access to psychological therapies

The Improving Access to Psychological Therapies (IAPT) programme involves a five-step approach to psychological care for people with depression and anxiety within the National Health Service (NHS) mental health services [22]. Stepped care models match treatment intensity to client needs by providing the least intrusive and most effective intervention for the client upon entering services. This allows for the effective management of resources, thus increasing access [23].

Step 2 of IAPT allows access to evidence-based treatments by delivering low-intensity psychological support to patients presenting with mild to moderate symptoms of depression and anxiety. These interventions are often delivered by Psychological Wellbeing Practitioners (PWPs), who are predominantly graduate psychologists with further training in delivering low-intensity CBT-based interventions [22].

A key aspect of the success of the IAPT model is its ability to report on outcomes. All services have a requirement to collect data on patients, access times, waiting times, dropout, treatment type, clinical outcomes, employment status, and work and social adjustment. Together, these outcomes collectively inform the success of the IAPT service.

As recommended by the National Institute for Health and Care Excellence [10, 11], the IAPT programme additionally offers computerised cognitive behavioural therapy (cCBT) as a low-intensity, Step 2 intervention for individuals presenting with mild to moderate symptoms of depression and/or anxiety. cCBT and internet-delivered cognitive behaviour therapy (iCBT) are delivered by PWPs, whose support is offered by means of electronic or telephone communication. Digital services in IAPT have been implemented at step 2 to help overcome the common barriers to accessing mental health treatment, such as costs and long waiting lists. There is certainly room for significant growth in these much-needed digital applications in IAPT, as digital use for treatment purposes is at less than 2% [24].

There is now a substantial body of research that supports the efficacy of online delivered CBT for depression and anxiety disorders [25–27] and findings have been transferred into clinical practice. This presents an opportunity to examine the effectiveness of iCBT in a natural setting.

### Cost effectiveness of iCBT

Early cost-effectiveness studies suggested that there could be large public health savings with the use of cCBT for treating depression and anxiety in mental health services [28]. In fact, the National Institute for Health and Care Excellence recommended the use of computerised CBT interventions partially based on this data [10, 11].

A recent systematic review of economic evaluations of internet-delivered interventions for mental health highlighted that interventions for depression and anxiety demonstrated cost-effectiveness compared to unguided interventions, waiting list controls, treatment as usual, group CBT, and telephone counselling [29]. The authors also make a call for future studies to firmly establish the cost-effectiveness of internet-delivered interventions.

### Mechanisms of change in iCBT

Understanding the factors that account for therapeutic changes is a key factor in providing the best patient care and assists in the pathway toward improving psychological treatments [30]. Despite the large body of research on mechanisms of change in traditional CBT, little has been achieved to date in understanding the mechanisms that drive change and their relative contribution to outcomes in iCBT [31]. Mechanisms of change comprise both general and specific factors: general factors include elements such as the therapeutic alliance, credibility of treatment, and belief about the potential of the intervention; specific factors include cognitive or meta-cognitive mechanisms, such as change in dysfunctional attitudes or repetitive negative thinking styles, improvement in emotion regulation abilities, cognitive and behavioural treatment skills usage, and therapist behaviours [32].

#### Aims

The overarching aim of the present study is to implement and evaluate the long-term effectiveness & cost-effectiveness of internet-delivered interventions for depression and anxiety disorders within IAPT services. The specific research questions include the following:Are the SilverCloud *Space from Depression and Space from Anxiety* internet-delivered interventions in IAPT effective in treating depression and anxiety disorders, and maintaining outcomes at follow-up, compared to waiting-list groups?Are the SilverCloud *Space from Depression and Space from Anxiety* internet-delivered interventions cost-effective in treating depression and anxiety disorders in IAPT?Are mediators/mechanisms of change and maintenance associated with both post-treatment and long-term effectiveness of internet-delivered interventions for depression and anxiety?

We hypothesize that: a) the iCBT interventions will be more effective than the waiting-list group in treating depression and anxiety disorders; b) the iCBT interventions will be cost-effective compared to the waiting-list group in treating depression and anxiety; c) we expect that mediators/ mechanisms of change including, repetitive negative thinking styles, emotion regulation skills, therapeutic alliance, credibility and expectancy in iCBT, CBT skills usage and therapist behaviours will be identified as positively impacting post-treatment outcomes and maintenance of gains in iCBT.

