#### Trial design

A parallel-groups, randomised controlled trial design will be used to examine the effectiveness and cost-effectiveness of internet-delivered interventions for depression and anxiety disorders against a waiting list control group. Based on the primary diagnosis obtained from the Mini International Neuropsychiatric Interview 7.0.2 (M.I.N.I), participants will be randomised into one of two groups: one for depression and another for anxiety.

Randomisation will follow a 2:1 ratio. For ethical reasons, participants in the control group will receive access to the internet intervention after the waiting list period (8 weeks). The study will be conducted following the CONSORT statement [33], the CONSORT extension for web-based interventions (CONSORT-EHEALTH) [34] and the SPIRIT guidelines (Standard Protocol Items: Recommendations for Interventional Trials) [35]. The SPIRIT checklist can be found in Additional file 1. The study protocol, information on the study, informed consent, and trial related documents have been submitted and approved by the NHS England Research Ethics Committee [REC Reference: 17/NW/0311]. The study flowchart is shown in Fig. 1.

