#### Waiting list control group

Participants in the waiting list control group receive no treatment for the duration of the first 8-weeks. At week 8, waiting-list participants will complete the primary and secondary outcome measures and begin their treatment with support from a PWP.

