#### Dropout measure

Finally, a *dropout questionnaire* will assess participants’ reasons for dropout from treatment. It includes only one open question asking for details about the specific reasons for dropout.

The study measures and assessment times are summarised in Table 2.

**Table 2 Tab2:** Study measures and assessment times

Measure	Assessment	Time of assessment
M.I.N.I. 7.0.2 for DSM-5	Diagnosis	BL and 3-FU
PHQ-9	Depression	BL, contin, Post-T, FU
GAD-7	Anxiety	BL, contin, Post-T, FU
IAPT Phobia Scale	Specific Phobia	BL, contin, Post-T, FU
WSAS	Functioning	BL, contin, Post-T, FU
SPIN	Social Phobia	BL, Post-T, FU
HAI	Health anxiety	BL, Post-T, FU
PSWQ	GAD	BL, Post-T, FU
PDSS	Panic	BL, Post-T, FU
EQ-5D-5 L	Health status	BL, Post-T, 6-FU, 9-FU, 12-FU
ReQol-10	Recovering quality of life/ mental wellbeing	BL, Post-T, 6-FU, 9-FU, 12-FU
CSRI	Resource utilisation	BL, Post-T, 6-FU
PEQ	Patient experience	Post-T
STAR-C	Therapeutic alliance	Throughout treatment, at each review of client
STAR-P	Therapeutic alliance	Throughout treatment, after each progress review with clinician
PBRS-A	Repetitive Negative Thinking	BL, week 4, Post-T, 3-FU
ERQ	Emotion Regulation	BL, Post-T
FATS	CBT-related skills usage	FU
Therapist behaviours checklist	Therapist behaviours	During treatment at review of client
Expectancy / credibility	Expectancy and credibility with the intervention	BL, week 4, Post-T
Dropout questionnaire	Reasons for dropout	3-FU

*BL* Baseline, *Post-T* Post-Treatment, *FU* All follow-ups, *3-FU* 3-month follow-up, *6-FU* 6-month follow-up, *contin* continuous, *PHQ-9* Patient health questionnaire-9, *GAD-7* Generalized anxiety disorder-7, *WSAS* Work and social adjustment, *SPIN* Social Phobia Inventory;` *HAI* Short health anxiety inventory, *PDSS* Panic disorder severity scale-self report, *PSWQ* Penn state worry questionnaire, *EQ-5D-5 l* EuroQol-5 Dimension-5 level, ReQoL-10 Recovering quality of life – 10 item version, *CSRI* Client services receipt inventory, *PEQ* Patient Experience questionnaire, *PBSR-A* Positive Beliefs about Rumination Scale – Adapted Version, *FATS* Frequency of Actions and Thoughts Scale, *ERQ* Emotion Regulation Questionnaire

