### Statistical analysis

The effectiveness of the internet-delivered interventions compared to control will be analysed using the intention to treat (ITT) approach. Participation levels will be monitored throughout the study and reasons for withdrawal or non-compliance of study subjects will be recorded to document bias associated with non-random protocol deviations. Any potential imbalances will be reported and considered fully in interpretation of the trial results. Missing data will be evaluated for randomness and imputed using multiple imputation procedures.

Differences in baseline primary and secondary outcome measures between treatment groups and waiting list control groups will be identified using χ^2^ tests for categorical variables and ANOVAs or t-tests for continuous variables. Efficacy of treatments over time will be measured using mixed effects models. To complement the post-hoc comparisons, the magnitude of change within and between the groups on the primary and secondary outcomes measures will be established using Cohen’s *d* statistic. Bonferroni corrected *p*-values will be reported for multiple comparisons. All statistical analyses will be conducted in SPSS, SAS and R. Results will be presented following CONSORT guidelines for reporting parallel group randomised trials.

The established IAPT definitions of recovery will be used in our analysis, where ‘recovery’ is determined by patients moving from ‘caseness’ at the beginning of the intervention (i.e. scoring ≥9 on the PHQ-9 or ≥8 on the GAD-7) to ‘non-caseness’ at the end of treatment (thus scoring below the cut-off). Two further established measures will be considered: *reliable improvement*, where the patient has a significant decrease in their PHQ-9 / GAD-7 score upon completion of their course of treatment; and *reliable recovery*, where the patient meets the criteria for both recovery and reliable improvement. Thus, a patient who moves from caseness to non-caseness, and does so by showing a significant decrease in their symptom scores, is said to have a reliable recovery [44].

Exploratory analyses, including the use of correlation and multiple regression, will be conducted to explore the role that mechanisms of change and maintenance measures play in the benefits obtained from the interventions. Moderation and mediation analyses may include the use of macros for SPSS and/or bootstrapping for exploring the role that mechanisms of change play on the outcomes.

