## Discussion

Internet-delivered interventions have evolved in the past years. Today we have robust technology platforms that can configure and deliver a range of intervention modules to meet the needs of the patient. SilverCloud Health is a global provider of mental health and wellbeing solutions online, and Berkshire NHS trust has been using SilverCloud interventions which were developed alongside clinicians at IAPT, and are NICE approved and suitable for use at Step 2.

Undertaking the principal aim of this trial will allow for a robust test of the effectiveness of iCBT in treating depression and anxiety symptoms, and the maintenance and cost-effectiveness of these treatment effects in the long-term. Positive results of these main outcome measures will allow iCBT to consolidate itself as not only a valid treatment option, but as an essential component to the care management pathway offered throughout all IAPT services. This should support the expansion of SilverCloud programmes as the leader in the delivery of digital interventions at Step 2 of IAPT. However, the relevance of the results will also likely have implications for the implementation and success of digital interventions for depression and anxiety in health and mental health care systems worldwide.

Investigating potential mediators and moderators of change will contribute to our understanding of key processes in achieving improvement using online-treatments for anxiety and depression. Mediators and moderators of iCBT outcomes have been relatively understudied, but exploring the roles of constructs such as rumination, emotion regulation, therapeutic alliance and CBT skills usage will provide insight into clinical change. This will potentially inform the tailoring of interventions to best address the needs of the targeted population, ultimately leading to the development of more effective treatments.

The proposed economic analysis will add to the current empirical literature in regards to evidence of the cost-effectiveness of internet-based mental health interventions (i.e. iCBT) and will be an innovative analysis of the SilverCloud iCBT interventions. In a context of health care provision where resources are already stretched, cost-effective interventions can only support the delivery of effective mental health services.

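### Research question 1 asks for maintenance at follow-up compared with waiting list, but the waiting list ends at week 8, so no later assessment has an untreated comparator

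*Protocol article*

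**What the plan says.** All places are in the protocol article.

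- **Aims.** The overarching aim is to "implement and evaluate the long-term effectiveness & cost-effectiveness of internet-delivered interventions". Research question 1 asks whether the programmes are "effective in treating depression and anxiety disorders, and maintaining outcomes at follow-up, compared to waiting-list groups".
- **Abstract, Methods.** "Participants in the waitlist control group will complete measures at baseline and week 8, at which point they will receive access to the treatment". Assessments are otherwise listed at baseline, during and at the end of the 8 weeks, and at 3, 6, 9 and 12 months.
- **Waiting list control group.** "At week 8, waiting-list participants will complete the primary and secondary outcome measures and begin their treatment with support from a PWP". Trial design gives the same 8-week limit and an ethical reason for it.
- **Table 2.** The diagnostic interview is scheduled at baseline and the 3-month follow-up only: "M.I.N.I. 7.0.2 for DSM-5 Diagnosis BL and 3-FU". The table does not separate the arms.
- **Statistical analysis, clinical part.** "Efficacy of treatments over time will be measured using mixed effects models". Nothing there limits the comparison with waiting list to week 8 or calls the follow-up results uncontrolled.
- **Statistical analysis, economic part.** The control horizon is given as 8 weeks and the intervention horizon as 12 months. Outcomes beyond week 8 are treated as extrapolated. The same paragraph also speaks of health-utility data being collected up to 12 months in both arms.
- **Risk management.** Scores on the PHQ-9 and GAD-7 at the end of the supported period determine discharge or referral for further treatment.
- **Discussion.** The study is expected to "allow for a robust test of the effectiveness of iCBT in treating depression and anxiety symptoms, and the maintenance and cost-effectiveness of these treatment effects", and the sentence places this in the long term.

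**The concern.** A comparison with waiting list needs people who are still waiting. After week 8 there are none, so the follow-up half of question 1 has no comparator of the kind it names. This is not an analysis detail that a statistical analysis plan could supply, because no method recovers an untreated group that has been treated.

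What is at stake is the conclusion the trial may draw. Entry requires raised scores (Table 1: PHQ-9 of at least 9 and/or GAD-7 of at least 8), so some later improvement is expected from regression to the mean and natural recovery. Some participants will also be referred on for further treatment because of their post-treatment scores. Stable scores in the iCBT arm from 3 to 12 months would mix all of this with any lasting effect of iCBT. Read against question 1 and the Discussion, such stability could be reported as a maintained effect relative to waiting list, which the design does not show.

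**Working it through.** **1. The plan's own figure.** Sample size gives 144 per diagnostic arm (96 treated, 48 waiting list) for d = 0.5, power 80%, alpha 0.05 and 2:1 allocation. With a two-sided test,

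control n = (1 + 1/2) × (1.960 + 0.842)² / 0.5² ≈ 1.5 × 7.849 / 0.25 = 47.1, rounded up to 48; treated n = 2 × 48 = 96; total 144.

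This matches; power by the noncentral t distribution is 80.2%. The trial is thus sized for one between-group difference against waiting list. The concern changes no sample size.

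**2. When is there an untreated control?** From week 0 to week 8, by the Abstract, Trial design and Waiting list control group.

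**3. When are the later assessments?** The article does not say whether months are counted from baseline or from the end of treatment, so both are shown, taking 3 months as 13 weeks and 12 months as 52.

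| Assessment | Week, from baseline | Week, from end of treatment | Untreated control? |
|---|---|---|---|
| End of treatment | 8 | 8 | Yes |
| 3 months (includes M.I.N.I.) | 13 | 8 + 13 = 21 | No |
| 6 months | 26 | 8 + 26 = 34 | No |
| 9 months | 39 | 8 + 39 = 47 | No |
| 12 months | 52 | 8 + 52 = 60 | No |

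Follow-ups with an untreated comparator: 0 of 4. Repeat M.I.N.I. interviews with one: 0 of 1. Share of the observation period without one: (52 − 8)/52 = 44/52 = 85% counting from baseline, or (60 − 8)/60 = 52/60 = 87% counting from the end of treatment.

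**4. Does any passage limit the claim?** The economic text does, by separating observed data (to week 8) from extrapolated outcomes (after it). The clinical text, research question 1 and the Discussion do not.

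**5. Are controls measured after week 8?** The Abstract lists baseline and week 8 for them. The economic text implies utility data to 12 months in both arms, yet also calls control outcomes beyond week 8 extrapolated. Table 2 does not distinguish the arms, and the flow diagram is not available in the text reviewed. The point is unresolved. Either way, controls measured later would be treated controls.

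**The case against.** The strongest defence is that the claim to be tested is narrower than question 1. Hypothesis (a) compares iCBT with waiting list and does not mention follow-up. Hypothesis (c) speaks of gains being maintained in iCBT, which reads as within the intervention. The Discussion does not say that maintenance is tested against waiting list. The 8-week limit has an ethical reason, the study is described as naturalistic, and service use is recorded with the CSRI at baseline, post-treatment and 6 months. All of this is fair, and it shows that the primary outcomes keep a sound randomised comparison at week 8. It does not correct question 1, which attaches the waiting-list comparison to follow-up. Nor does it qualify the Discussion's promise of a robust test: a treatment effect is a difference from a comparator, so its maintenance needs one too.

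Three stronger readings are tempting, and the article does not support them.

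- *That no randomised long-term comparison of any kind exists.* If controls are followed after week 8, as the economic text suggests, the arms could still be compared as randomised. That would be immediate versus delayed treatment, not iCBT versus waiting list.
- *That the mixed model will distort the week-8 result by forcing a straight line through time.* The article does not say how time enters the model, and that is commonly left to the analysis plan.
- *That the M.I.N.I. is scheduled wrongly.* Its described purpose is to establish diagnosis and allocate participants to a programme, and no section promises a randomised comparison of diagnostic remission. Placing the repeat at 3 months is a trade-off, not an error. What follows is only that its result is uncontrolled.

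**Conclusion.** The point holds for the comparison that question 1 names. None of the four follow-ups and no repeat M.I.N.I. has an untreated comparator, and about 85% to 87% of the observation period lies after the waiting list ends. This rests on the stated week-8 start of treatment for the control group. The percentage depends on how months are counted; the count of 0 of 4 does not.

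The consequence is limited but real. The week-8 comparison on the PHQ-9 and GAD-7 stands, as does the sample size. What cannot stand is a claim that clinical gains at 3 to 12 months were maintained relative to waiting list, or that they are due to iCBT alone. The article already draws this line for costs and QALYs and should draw it for clinical outcomes.

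**What to change.** 1. In Statistical analysis, state that the randomised comparison of iCBT with waiting list on clinical outcomes is at week 8 only.
2. Reword research question 1 and the Discussion sentence so that maintenance from 3 to 12 months, and the 3-month M.I.N.I. result, are uncontrolled within-group descriptions that cannot be attributed to iCBT alone. Report treatment received by referral after the supported period alongside them. The CSRI as scheduled in Table 2 stops at 6 months, so say which source covers months 6 to 12.
3. Reconcile the Abstract (control measures at baseline and week 8) with the economic text (data to 12 months in both arms). If controls are followed after week 8, label any later between-arm comparison as immediate versus delayed treatment.

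The cost is mainly wording, plus reporting of later treatment. No visit, treatment, interview time or sample size changes. The sponsor gives up a long-term comparative claim that the design could not support.
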